### Data collection

The study will acquire approval from the Ministry of Health in Saudi Arabia to ensure no school-based dental program is implemented in the selected schools and to utilize the ministries staff and information technology facilities (Mawid, Sehhaty, and ANAT applications). Also, approval from the Ministry of Education will be obtained to both access schools and to obtain a list of schools in Riyadh city.

Following obtaining the approvals, the principal investigators will send an invitation to the selected schools. Schools that refuse to participate or do not reply will be replaced with randomly chosen new school from the same list obtained. For schools that agree to participate, the principal investigator will arrange a date and time for data collection by meeting with the head of the schools.

All children eligible to participate in the schools that agree to participate will receive a booklet that includes an information sheet a written and consent form to both children and their parents. A text message from the school administration will be sent on the same day informing the parents about the booklet and encouraging them to participate. After 1 week, a reminder text message will be sent to parents who did not send the forms back and an acknowledgment text will be sent to those agreeing to participate.

After obtaining signed consent from both parents and their children, the team will book a clinical examination appointment to the children through (Mawid). Parents will receive an SMS message confirming the appointment.

On the day of the booked clinical examination, the parents will be asked to fill structured questionnaire while their children are being examined. The parental questionnaire has been modified from the WHO questionnaire for assessment of oral health status to collect data on sociodemographic characteristics (child’s age and gender, school, household size, parental education and family income), data on dental visit oral hygiene perception and behavior, oral health impact on quality of life, and diet. The questionnaire will be deiminated with every follow-up clinical examination (+ 3 months, + 6 months, + 12 months + 24 months, + 36 months from baseline).

A total number of 40 dental hygienists will be included in this trial under the supervision of the principal investigator. Twenty dental hygienists performing the clinical examination in the Ministry of Health Primary Health Care Centres will be trained and calibrated before the beginning of the trial. The other 20 dental hygienists will be responsible for virtual supervised tooth brushing where two dental hygienists be assigned to each school (2:1 ratio).

Clinical examination for caries experience will be performed according to the WHO criteria that define dental caries at caries into dentine threshold [29]. No radiographs will be taken. Examination will be conducted similarly at baseline and all following follow-ups (+ 3 months, + 6 months, + 12 months + 24 months, + 36 months from baseline). Examination will be performed in a dental clinic on dental chair using an examination kit that includes a plane mouth mirror and a periodontal probe. Teeth will not be brushed or cleaned prior to the examination as plaque score is an outcome of interest. During the examination, air will be applied to better assess the plaque; this will be followed by removal of debris using gauze and cotton roll to facilitate visual inspection and assess gingival score and dental caries. Standard infection control will be in place.

After each clinical examination phase (baseline, (+ 3 months, + 6 months, + 12 months, + 24 months, + 36 months), 10% of children will be re-examined to assess inter-examiner reliability. Children with identified positive caries will be informed, and parents will be instructed to book an online appointment through Mawid. Given the training in oral health condition assessment, the probability of false positive caries cases is minimal. Yet, upon the booked appointment by the parents, a standard dental check-up is always conducted as part of the treatment plan where any false-positive cases will be identified. If that is the case, the dentist will inform the parents that no further treatment is required.

### Ensuring participants’ retention

Given that this is a 36-month trial, with different points of data collection (baseline, + 3 months, + 6 months, + 12 months + 24 months, + 36 months), and the two final follow-ups will be collected over two separate academic years. This implies that there might be some losses in follow-ups as children may change their schools/residences. We have increased the trial size to compensate for 20% attrition rate (i.e., derived from the proportion of children continuing in the same school the following academic year). That aside, we expect a high completion rate as parental consent will be sought for all waves of data collection simultaneously.

### Data storages and management

The principal investigator will be responsible for all data entry and management. Personal identifiable information will be collected to regain contact with the child for the follow-up assessments and link different points of data collected for the same child. This will be handled by a pseudo-anonymization where the principal investigator will keep a separate file that includes all personal identification information for all children participating in the trial. An artificial identifier (code) will be assigned to each child as they enter the study. Thus, all involved in the trial will be working with coded data when collecting or analyzing information.

Only the codes will be used in data entry without any identifiable personal information. A protected device (university desktop) assigned to the principal investigator will be used to enter the coded data as long as the data collection progresses. It is worth noting that consents, assents, and questionnaires will be collected electronically, whereas oral assessment forms will be filled manually through investigators. All electronic forms and questionnaires will be collected through Microsoft Forms empowered by KSU online drive and will be stored in the same drive. Upon completion of the data collection, all electronic files (consents, Assents, and questionnaires) will be transferred to a password-protected desktop computer, and all printed forms (oral assessment forms) will be transferred to a locked cabinet and both located at the College of Applied Medical Sciences at KSU. Only the authorized team members will grant access to the study data.

### Data analysis justification of sample size

Sample size was calculated based on the prevalence of untreated dental caries (84%) reported in a previous study by Adam and his colleagues (2022) among Riyadh children [31]. Considering a 95% confidence interval and 80% power, 690 children (354 individuals per arm) were sufficient to detect a clinically significant difference of 10% with design effect of two arms over a period of 36 months. The design effect was calculated as 1.44, based on an intra-class correlation coefficient of 0.02 derived from a previous study [32]. After accounting for clustering, the required number of clusters would be 20 schools and an average cluster size of 50 participants. Allowing for up to 20% dropout rate upon follow-up time, 1192 participants are required (596 per arm) [33].

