Supervision by adults while the children brush their teeth can ensure that they have enough exposure to fluoride toothpaste each day [11]. There may also be unintended educational consequences. Children that are supervised might learn how to brush their teeth more effectively [15]. Children might place more priority on oral health and develop better oral health behaviors in general. They might also enhance the quantity and frequency of daily tooth brushing. Finally, surveillance while brushing may have an impact on children through a form of prolonged Hawthorne effect [16], causing them to change their oral health self-care behaviors in reaction to the knowledge of being watched.

Supervised tooth brushing programs are implemented throughout the world to provide young children’s developing teeth with additional fluoride as a form of dental caries prevention. Numerous published research studies have demonstrated the value of supervised tooth brushing programs in schools [15, 17–21]. For instance, Clark et al. (2019) [17] studied children from Northland, New Zealand, aged 10 to 13, and found that those who received the supervised school tooth brushing intervention had significantly reduced caries prevalence than those who did not. This is a quasi-experimental study. At baseline, all children received routine dental examinations, including bitewing radiographs and the ICDAS to record dental caries. A supervised tooth brushing program was implemented for half of the children. Exams were given again at the end of the school year. There were 335 children at the start, with 240 (71.6%) being followed up on. Caries was found in 7.3% of the tooth brushing group and 71.5% of the control group. Similarly, a randomized controlled trial recruiting primary school children in Northwest London compared the variances in caries increment between a group that received teacher-supervised tooth brushing with a fluoride toothpaste at 1450 parts per million (ppm) once a day at school and a non-intervention group. It concluded that the intervention group had a statistically significant lower caries incidence compared to the control group (2.60 versus 2.92; 10.9%; *p*-value < 0.001) [18]. These findings suggest that implementing preventative measures in schools can be an efficient approach to improving oral health.

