#### Primary outcome

The study’s primary outcome is the change in caries experience—the number of decayed (untreated dental caries) missing and filled teeth—in both primary and permanent teeth over 36 months. The underlining assumption of the selected primary outcome is that children in the intervention group will be exposed to more fluoride (toothpaste daily exposure) in addition to mechanical tooth cleaning (correct dental plaque debridement through correct brushing technique) during the trial period leading to a fewer incidence of dental caries than those in the control group.

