### Between groups comparisons

Stata version 17 will be employed for data analysis. In a comparison of demographic (sex, gender), socioeconomic (family income, parental education), behavioral characteristics (tooth brushing frequency, usage of fluoride toothpaste, dental attendance pattern, impact of oral health on daily living, sugar intake), and caries, plaque and gingival level in both primary and permanent teeth, the difference between both intervention groups will be carried out using chi-square test for categorical variables and a *t*-test for continuous variables.

We will be reporting absolute and relative measure effect, that is, absolute and relative difference in mean for continuous outcomes (changes in the number of untreated caries) and risk difference and relative risk for categorical outcomes (changes in brushing frequency, changes in plaque and gingival conditions, changes in impact of oral health on daily living). For the primary outcome (changes in the number of untreated dental caries), negative binomial regression will be used to estimate relative difference (incidence rate ratio) and predictive margin to estimate absolute difference between intervention groups. The applied analytical technique will allow accounting for stratification of the sample and clustering of children within schools and any baseline socioeconomic difference between intervention groups. For the secondary outcome, multinomial regression will be used to estimate relative risk for the changes in frequency of daily tooth brushing and changes in the perceived oral health on child’s daily life. Predictive margins will also be used to estimate absolute difference in each secondary outcome. Intention-to-treat analysis will be used to handle missing values in all outcomes.

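### The 80% power is calculated for a prevalence of untreated caries, not for the primary outcome, which is a 36-month change in a tooth count

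*Protocol article*

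**What the plan says.** Under Data analysis justification of sample size, the protocol article states "Sample size was calculated based on the prevalence of untreated dental caries (84"%). It continues: "Considering a 95% confidence interval and 80% power, 690 children (354 individuals per arm") were "sufficient to detect a clinically significant difference of 10"%. Whether the 10% is absolute or relative is not said. For clustering, "The design effect was calculated as 1.44, based on an intra-class correlation coefficient of 0.02", and "the required number of clusters would be 20 schools and an average cluster size of 50 participants". A 20% dropout allowance brings the total to 1192 (596 per arm).

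Under Primary outcome, the measure is the change over 36 months in "the number of decayed (untreated dental caries) missing and filled teeth", in primary and permanent teeth. The Abstract and Discussion agree. Under Between groups comparisons, "negative binomial regression will be used to estimate relative difference (incidence rate ratio"), with predictive margins for the absolute difference. That section calls the outcome the change in the number of untreated carious teeth rather than decayed, missing and filled teeth, but in both wordings it is a count.

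The Secondary outcomes are plaque and gingival scores, brushing frequency and perceived impact on daily life. The proportion of children with untreated caries is not among them. The Background cites a London trial of teacher-supervised brushing that found a "lower caries incidence compared to the control group (2.60 versus 2.92; 10.9"%).

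**The concern.** The calculation and the primary analysis concern different quantities. The power of a two-proportion comparison depends on the two proportions. The power of a negative binomial comparison depends on the mean count, the overdispersion and the rate ratio, and the sample size section gives none of these. The two measures can also move separately. Both arms are referred for free treatment, and a decayed tooth that is filled or extracted leaves the untreated-caries measure but stays in the decayed, missing and filled count.

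A reader would take the trial to have 80% power for a 10% effect on caries increment. If the result is null, it could be read as adequately powered evidence against the programme, and the article says its findings should inform policy on school programmes.

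**Working it through.** **1. Reproducing the plan's figure.** Inputs from the sample size section: 84%, a 10% difference, 80% power and a 95% confidence level (two-sided 5% assumed). Formula per arm: n = (1.96 + 0.8416)² × [p1(1−p1) + p2(1−p2)] / (p1−p2)².
- Relative 10% (84% vs 75.6%): 354.7, matching the stated 354.
- Absolute 10% (84% vs 74%): about 257, no match.
- Total: 690 × 1.44 × 1.2 = 1192.3, matching 1192.

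The calculation is therefore a two-proportion one, and the 10% was most likely relative.

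**2. What it contains.** Two proportions, an ICC, a design effect and a dropout rate. There is no count mean, standard deviation, dispersion or rate ratio.

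**3. Illustration for the count.** Inputs:
- Means 2.92 and 2.60 from the cited London trial (Background). Using them as this trial's 36-month means is an assumption; the article does not give that trial's follow-up time or counting unit.
- Completers: 1192 × 0.8 ≈ 954, or 476.8 per arm and 47.7 per school in 20 schools.
- Design effect with ICC 0.02: 1 + (47.7 − 1) × 0.02 = 1.93. The protocol states 1.44, so both are shown.
- Dispersion k: not given anywhere, so a range is assumed.

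Effective size per arm: 476.8/1.934 = 246.5, or 476.8/1.44 = 331.1.

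SE(log RR) = √[(1/2.92 + 1/2.60 + 2k)/n_eff]; |ln(2.60/2.92)| = 0.1161; power = Φ(0.1161/SE − 1.96).

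| k (assumed) | Power, design effect 1.93 | Power, design effect 1.44 |
|---|---|---|
| 0 (no overdispersion) | 57% | 70% |
| 0.1 | 47% | 59% |
| 0.25 | 38% | 48% |
| 0.5 | 28% | 36% |
| 1.0 | 20% | 25% |
| 2.0 | 13% | 16% |

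At k = 0.25 and design effect 1.93, for example, SE = 0.0705, the ratio is 1.645, and Φ(−0.315) = 38%.

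**4. Cross-check as a difference in means.** With a difference of 0.32, 954 completers and design effect 1.93, assumed SDs of 1.5, 2, 3 and 4 give 66%, 43%, 22% and 14%. The highest value with the stated 1.44 is 78%, at SD 1.5.

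**5. Detectable rate ratio at 80% power.** exp(−2.80 × SE), design effect 1.93: 0.82, 0.79 and 0.75 at k = 0.25, 0.5 and 1.0, a reduction of about 18% to 25%. With 1.44: 0.84, 0.82 and 0.78.

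**6. Sensitivity to effect and mean.** A 24% reduction (the figure the Background gives for fluoride toothpaste), with control mean 2.92 and design effect 1.93, gives 97%, 90%, 73% and 50% at k = 0.25, 0.5, 1 and 2. Keeping the ratio at 0.89 but assuming a control mean of 6 at k = 0.25 raises power from 38% to about 50%.

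**The case against.** The strongest reply is that any power figure for the count is the reviewer's construction. Dispersion is assumed, the mean is borrowed, and the 10.9% effect is one of several that the article cites. This stands. A reader might infer that the trial's real power is 20% to 38%. The document does not support that as an unconditional statement: the range follows from k between 0.25 and 1.0 and a design effect of 1.93, whereas the protocol states 1.44. The gap between 1.44 and what ICC 0.02 implies is a separate matter.

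The other cited effects do not rescue the claim. The 24% concerns fluoride toothpaste, and both arms here receive it. The 7.3% against 71.5% comes from a quasi-experimental study of prevalence. The London trial is the closest randomised comparison, although it tested daily supervision in school, not weekly virtual sessions with videos for three months.

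Two further inferences are tempting and do not hold:
- That brushing could not lower a proportion already at 84%. The plan compares arms, not children with their own baseline. Both arms are offered free treatment, and new lesions over 36 months could separate the arms.
- That nothing in the plan tests prevalence. Between groups comparisons puts caries level in a list compared by chi-square or t-test. What can be said is that prevalence is not a named outcome.

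**Conclusion.** The mismatch is certain from the text: the stated 80% power belongs to a prevalence comparison of about 84% against 75.6%, and it does not apply to the primary count analysis. The size of any shortfall is conditional. At the means 2.92 and 2.60 with 954 completers, power is about 13% to 59% over assumed dispersion 0.1 to 2 and design effects 1.44 to 1.93. No case examined at these means, with that number of completers and those design effects, reaches 80%, even without overdispersion. Power would be higher with a larger mean count and could pass 80% with a larger effect. The finding is that the sample size is not justified for the primary outcome; it does not establish that the trial is too small for every plausible effect.

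**What to change.** Replace or supplement the prevalence calculation with one for the primary count. State the assumed 36-month mean increment, dispersion, ICC, design effect and target rate ratio, each with its source. Report the rate ratio that 20 schools and 1192 recruited children can detect with 80% power over a range of those assumptions. The 0.82 to 0.75 shown above, for dispersion 0.25 to 1.0 at a control mean near 2.9, is an example of the format and should not be adopted without sourced inputs. Withdraw the 80% power claim for the primary outcome, or label it as applying to prevalence only, and say whether the 10% is relative or absolute.

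The cost is a recalculation and a change of wording. No extra recruitment is needed for the correction. The drawback is that the stated detectable effect will probably look less favourable.

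### The sample-size chain contradicts its own inputs, chiefly a design effect of 1.44 where ICC 0.02 and 50 children per school give 1.98; the prevalence comparison falls below the stated 80% power

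*Protocol article*

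**What the plan says.** All the figures stand in the Protocol article, section *Data analysis justification of sample size*.

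- The calculation starts from an 84% prevalence of untreated caries, "Considering a 95% confidence interval and 80% power".
- The base size is given as "690 children (354 individuals per arm"), said to be "sufficient to detect a clinically significant difference of 10" per cent.
- Clustering: "The design effect was calculated as 1.44, based on an intra-class correlation coefficient of 0.02 derived from a previous study".
- Clusters: "the required number of clusters would be 20 schools and an average cluster size of 50 participants".
- The final size after a 20% dropout allowance is 1192, or 596 per arm.

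Two other sections bear on this. *Setting and participants* also fixes the number of schools at 20. *Ensuring participants' retention* says the trial was enlarged to compensate for 20% attrition.

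**The concern.** A reader who recomputes the paragraph cannot get from its inputs to its result. The ICC and cluster size do not give the design effect, the dropout step does not leave enough completers, the arm size does not match the total, and the target difference can be read in two ways. If the design effect is too small, 1192 children in 20 schools carry less information than the plan assumes, and the 80% power is not supported. That matters most if the trial shows no clear difference, because readers will judge such a result partly by the power the protocol claimed.

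**Working it through.** **Inputs (all from the sample-size section).** Control prevalence 84%; 5% level, taken as two-sided because only a 95% confidence interval is stated; power 80%; difference 10%; base 690 (354 per arm); ICC 0.02; design effect 1.44; 20 schools of 50; dropout 20%; final 1192 (596 per arm).

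**1. Reproducing the plan's total.**
- 690 x 1.44 = 993.6, and 993.6 x 1.2 = 1192.3. Per arm: 345 x 1.44 x 1.2 = 596.2.
- Both match the stated figures. The base carried forward is therefore 690 (345 per arm), not 354 per arm.

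**2. Design effect, 1 + (m - 1) x ICC.**
- m = 50: 1 + 49 x 0.02 = 1.98.
- m = 47.7 (completers per school, step 3): 1 + 46.7 x 0.02 = 1.93.
- Solving for 1.44: m = 0.44/0.02 + 1 = 23. At m = 50, 1.44 would need an ICC of 0.44/49 = 0.009, which does not round to 0.02.

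**3. Dropout.**
- To retain 993.6 children after 20% loss: 993.6/0.8 = 1242.
- 1192 x 0.8 = 953.6, about 954, which is 40 fewer than the 994 needed with the plan's own design effect.
- Completers per school: 953.6/20 = 47.7.

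**4. Arm sizes.** 2 x 354 = 708, not 690.

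**5. Which 10%?** Unpooled formula: n per arm = (z_alpha + z_beta)^2 x [p1(1 - p1) + p2(1 - p2)]/(p1 - p2)^2. The squared term is 7.849 at 80% power and 10.507 at 90%.
- Relative, 84% vs 75.6%, 80% power: 7.849 x (0.1344 + 0.1845)/0.084^2 = 354.7 (358 with the pooled-variance version).
- Absolute, 84% vs 74%, 80% power: 7.849 x (0.1344 + 0.1924)/0.10^2 = 256.5 (260 pooled).
- Absolute, 90% power: 10.507 x 0.3268/0.01 = 343.4 (347 pooled).

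So 354 fits the relative reading at 80% power, while the 345 per arm actually carried forward is close to the absolute reading at 90%.

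**6. Power delivered for the prevalence comparison.**
- Completers per arm: 953.6/2 = 476.8. Effective n per arm: 476.8/1.934 = 246.6.
- Absolute: SE = sqrt(0.3268/246.6) = 0.0364; 0.10/0.0364 = 2.75; 2.75 - 1.96 = 0.79.
- Relative: SE = sqrt(0.3189/246.6) = 0.0360; 0.084/0.0360 = 2.34; 2.34 - 1.96 = 0.38.

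| Difference | Normal: unpooled (pooled) | Sensitivity: t, 18 df (20 schools minus 2 arms) |
|---|---|---|
| 84% vs 74% | 78.4% (78.0%) | 73.8% |
| 84% vs 75.6% | 64.7% (64.3%) | 59.9% |

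**7. Which error costs the power?** Keeping 1.44 and applying only the 20% loss gives 476.8/1.44 = 331.1 effective per arm, and power (pooled) of 88.7% for 84% vs 74% or 76.9% for 84% vs 75.6%. The design effect is the main driver.

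**The case against.** The strongest reply is that the shortfall may be trivial. Next to a prevalence of 84%, a 10% difference is naturally read as 10 percentage points, and on that reading power is about 78%. At the planned 20 x 50 = 1000 children with a design effect of 1.98 (effective n 252.5 per arm), it is 79.4%. This stands. It holds, however, because 690 exceeds the 2 x 260 = 520 that this reading needs at 80% power, not because the chain is right.

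A reader might infer that the trial simply has 60-65% power, because 354 per arm fits the relative reading. The protocol does not support that. The figure carried through to 1192 is 345 per arm, which sits near the absolute reading at 90% power. Neither reading is established, so both powers must be shown.

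A reader might also blame all the errors alike. The mismatch between 690 and 354 is a reporting inconsistency and does not itself lower power. The dropout error alone leaves the absolute reading above 80%.

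Two further points stand. The t reference on 18 df is a reviewer's sensitivity check; the protocol names no such test. And every power above concerns the prevalence of untreated caries. The primary outcome is change in a tooth count, to be analysed by negative binomial regression (section *Between groups comparisons*). Its power may be higher or lower and cannot be derived from this document.

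Condensing a protocol into an article does not explain the contradictions, since the figures that conflict are all printed.

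**Conclusion.** The paragraph is wrong as written. The main error is the design effect: 1.98 at 50 per school (1.93 at 47.7 completers) against 1.44. The dropout step is a second, smaller error: 1242 against 1192 on the plan's own terms. The arm-size mismatch and the unlabelled 10% are reporting defects, though the second decides how large the shortfall is. Power for the prevalence comparison is below 80% on either reading: about 2 points below for 84% vs 74%, and about 15 points below for 84% vs 75.6%. The t-based check puts the gaps at about 6 and 20 points.

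These figures assume a two-sided 5% test, ICC 0.02, 20 schools of equal size and exactly 20% loss. They do not show that the trial is underpowered for its primary outcome. Nor do they fix a larger enrolment: holding 690 effective children at 50 per school would mean 690 x 1.98/0.8 = 1708 enrolled, but a base of 260 per arm on the absolute reading gives 520 x 1.98/0.8 = 1287.

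**What to change.** Rewrite the paragraph as one chain:

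1. Say whether the 10% is absolute (84% vs 74%) or relative (84% vs 75.6%).
2. Give one per-arm size and a total that is twice that size.
3. Use a design effect of 1 + (m - 1) x 0.02 at the expected completers per school.
4. Divide by 0.8 for dropout.

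Then state the power that 1192 children in 20 schools deliver under the chosen reading: about 78% for 84% vs 74%, or about 65% for 84% vs 75.6%. The t-based values (about 74% and 60%) can be added as a sensitivity check. Say that this power applies to the prevalence of untreated caries and not to the count-based primary outcome.

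The cost is a change of wording and a less favourable stated power. The restatement needs no extra schools or children.
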